## Abstract

**Background:**

Aerobic exercise is promising for preventing Alzheimer’s disease (AD) and AD-related dementia (ADRD), but exercise trials have shown mixed results. An important, understudied factor potentially contributing to mixed results is individual differences in aerobic fitness responses to moderate-intensity continuous training (MICT). This trial will test the effects and mechanisms of 6 months of aerobic exercise tailored on aerobic fitness response to MICT in community-dwelling older adults with early symptomatic AD. We aim to (I) test the effects of aerobic exercise on aerobic fitness, white matter hyperintensity volume (WMHv), and patient-centered outcomes in older adults with early symptomatic AD; (II) determine the best exercise to improve aerobic fitness and reduce non-responses over 6 months; and (III) examine the mechanisms of aerobic exercise’s action on cognition.

**Methods:**

This stage II trial is a Sequential, Multiple Assignment, Randomized Trial (SMART). The hypothesis is that MICT augmented with high-intensity interval training (HIIT) or combined aerobic and resistance exercise (CARE) will improve aerobic fitness, WMHv, and AD/ADRD plasma biomarkers. This trial will enroll 108 dyads (participants and their study partners). Participants (*n* = 108) are randomized using a 2:1 allocation ratio to 3-month MICT or 6-month stretching control. After the initial 3-month intervention period for participants assigned to MICT, aerobic fitness is measured with peak oxygen consumption (VO_2peak_) from a cycle-ergometer exercise testing and the shuttle walk test to identify non-response (< 5% increase). Non-responders are subsequently re-randomized (1:1) to either HIIT or CARE for 3 months. Responders continue MICT. All participants are followed for an additional 6 months post-intervention. Primary outcomes are VO_2peak_ measured at 0, 3, 6, 9, and 12 months and WMHv at 0, 6, and 12 months. Secondary outcomes include memory, physical function, behavioral and psychological symptoms of dementia (BPSD), quality of life (QoL), caregiver burden, and AD plasma biomarkers. This trial has 80% power, assuming 18% and 25% attrition at 6 and 12 months, respectively, to detect changes in aerobic fitness.

**Discussion:**

Individual differences in VO_2peak_ responses were reported in older adults with AD/ADRD previously but how this affects response to exercise interventions is unknown, Precision exercise tailored to VO_2peak_ is critical to advance exercise research in AD.

**Trial registration:**

ClinicalTrials.gov NCT05877196. Registered on May 25, 2023.

## Administrative information

Note: the numbers in curly brackets in this protocol refer to SPIRIT checklist item numbers. The order of the items has been modified to group similar items (see http://www.equator-network.org/reporting-guidelines/spirit-2013-statement-defining-standard-protocol-items-for-clinical-trials/).

## Introduction

### Background and rationale {6a}

Alzheimer’s disease (AD) cannot be cured and affects 6.2 million Americans, with estimates indicating it will affect 14 million Americans and cost > $1.1 trillion by 2050 [1]. Aerobic exercise is a promising intervention for preventing and treating AD but has shown mixed effects on clinical outcomes such as cognition [2], which is likely caused by an important, understudied factor—individual differences in aerobic fitness responses. Individual differences in fitness response to habitual moderate-intensity continuous training (MICT), long established in young adults [3–5], are more prominent in older adults [6]. Although trials in older adults with AD and related dementias (ADRD) showed a dose-response relationship between aerobic exercise and cognition [7–9], inter-individual differences in aerobic fitness response to MICT was first reported by the FIT-AD Trial [10]. Hence, precision exercise that focuses on individual differences [11–13] is needed with adaptive exercise such as high-intensity interval training (HIIT) and combined aerobic and resistance exercise (CARE) which have been shown to mitigate aerobic fitness non-responses among older adults without AD [14]. Moreover, animal studies [15] strongly support aerobic exercise modifying AD’s AT(N) biomarkers: Amyloid-beta (Aβ), Tau, and Neurodegeneration [16] though human studies are limited with conflicting findings [17–20].

### Objectives {7}

The purpose of this manuscript is to describe the study protocol for FIT-AD SMART, which aims to test the effects and mechanisms of 6-month aerobic exercise that is tailored on aerobic fitness response to MICT in community-dwelling older adults with early symptomatic AD. FIT-AD refers to Function Improvement through aerobic exercise Training in older adults with AD and SMART refers to Sequential, Multiple Assignment, Randomized Trial design. The FIT-AD SMART was built on findings from the FIT-AD Trial that showed individual differences in aerobic fitness responses to MICT to:Aim I. Test the effects of aerobic exercise on aerobic fitness, white matter hyperintensity (WMHv), and patient-centered outcomes in older adults with early symptomatic AD. H1a: Aerobic exercise (MICT, MICT + HIIT, MICT + CARE) will increase aerobic fitness and reduce WMHv over 6 and 12 months more than stretching. H1b: Aerobic exercise will improve patient-centered outcomes over 12 months in comparison to stretching.Aim II. Determine the best exercise to improve aerobic fitness and reduce aerobic fitness non-responses over 6 months in older adults with early symptomatic AD. H2a: MICT + HIIT improves aerobic fitness the most, followed by MICT + CARE, then MICT only, and then stretching. H2b: HIIT reduces the number of MICT non-responders more than CARE.Aim III. Examine the mechanisms of aerobic exercise’s action on memory in early symptomatic AD. H3: Changes in plasma Aβ_42/40_, phospho-tau181 (ptau181), total tau (t-tau), and neurofilament light chain (NfL) mediate memory responses to exercise.

### Trial design {8}

FIT-AD SMART is a single-site Stage II (according to the NIH Stage Model) sequential, multiple assessment, randomized trial. One hundred and eight (*n* = 108) of community-dwelling older adults with early symptomatic AD are randomized using a 2:1 allocation ratio (randomization 1) to 3-month MICT or 6-month stretching control, after baseline data collection. Their primary family caregivers are also enrolled as study partners. VO_2peak_ is re-assessed at the end of 3 months and is used to identify non-responders (defined in the Methods section) in participants assigned to the MICT group. Non-responders are subsequently re-randomized on a 1:1 allocation ratio to either HIIT or CARE for 3 months (randomization 2). Responders continue MICT for another 3 months (Fig. 1). Both randomizations are stratified by baseline age (66–75, 76–85, 85 + years) using random permuted blocks of 3 and 6. Study outcomes are assessed at 0, 3, 6, 9, and 12 months by trained data collectors who are blinded to group allocation.

**Fig. 1 Fig1:**
[figure not shown]
The FIT-AD SMART design

## Methods: participants, interventions, and outcomes

### Study setting {9}

The FIT-AD SMART is a single-site trial. Screening, exercise testing, blood collection and storage, and non-MRI data collections occur on the Downtown Campus of Arizona State University (ASU), located in Phoenix, AZ. Exercise sessions are delivered in local gyms such as YMCAs or in senior communities. MRI is obtained at Banner Alzheimer’s Institute and other Banner facilities when a larger physical size of the MRI machine is needed.

### Eligibility criteria {10}

Early symptomatic AD is defined as mild cognitive impairment (MCI) and mild AD dementia using the 2011 criteria [21] through reviews of medical records (lab, notes, cognitive testing), screening cognitive test, health history, and MRI. The criteria for MCI include [1] 21 ≤ Montreal Cognitive Assessment (MoCA) score ≤ 26 (education-corrected), [2] Functional Activities Questionnaire (FAQ) < 9, [1] absence of dementia, [2] cognitive impairment not due to other causes, including major neurologic, psychiatric, and substance abuse disorders, e.g., Parkinson’s disease, head trauma, cortical stroke, major depression, and alcohol abuse, and [3] lack of MRI evidence indicating normal pressure hydrocephalus, brain tumor, subdural hematoma, significant post-traumatic encephalomalacia, and one or more large cortical infarction. The criteria for mild AD dementia include (1) insidious onset and clear-cut history of worsening cognition that interferes with ability to function at work or at usual activities by self/family report or observation, (2) decline from previous levels of functioning by self/family report or observation, (3) 11 ≤ MoCA score < 21, (4) FAQ ≥ 9, (5) cognitive impairment not due to other causes, including major neurologic, psychiatric, and substance abuse disorders, e.g., Parkinson’s disease, non-AD dementia, head trauma, cortical stroke, major depression, and alcohol abuse, and (6) lack of MRI evidence indicating normal pressure hydrocephalus, brain tumor, subdural hematoma, significant post-traumatic encephalomalacia, and one or more large cortical infarction. The eligibility criteria for both participants and study partners are detailed in Table 1.

**Table 1 Tab1:** Eligibility criteria

Inclusion criteria	Exclusion criteria
**Older adults with early symptomatic Alzheimer’s disease (AD)**	
o Early symptomatic AD (mild cognitive impairment or mild AD dementia [probable or possible]) o Community-dwelling o ≥ 65 years old o Verified exercise safety o Having a qualified study partner o Volunteering to donate 18 mL blood 5 times o Verified MRI safety	o Resting heart rate ≤ 50 or ≥ 100 bpm due to arrhythmia after 5-min quiet resting o American College of Sports Medicine exercise contraindications, e.g., acute myocardial infarctions o New or unevaluated signs, symptoms, or diseases o Abnormal findings during symptom-limited cycle-ergometer test o Enrollment in another intervention aimed at improving cognition o Moderate to strenuous exercise > 150 min a week in the previous 6 months o Geriatric depression scale-15 ≥ 9, on ≥ 2 anti-depression medications, or poorly managed or unstable depression o Generalized Anxiety Disorder-7 ≥ 10
**Inclusion criteria for study partners**	
o 18 years old or older o Contact with the participant ≥ 2 times per week for ≥ 6 months o Know the participant’s memory status and ability to perform daily activities such as managing money, driving, shopping, and preparing meals o Consent to participate	

### Who will take informed consent? {26a}

During in-person interview, the study staff trained to conduct consent will assess decisional capacity of participants and obtain informed consent from participants and their study partners.

### Additional consent provisions for collection and use of participant data and biological specimens {26b}

Efforts will be made to limit the use and disclosure of participants’ personal information, including research studies and medical records, to people who need to review this information. All collected data such as demographic, physical, and mental data, brain scan, and blood specimens will be de-identified. De-identified data will be stored on a secure database and blood specimens in − 80° freezer at ASU. These de-identified data may be shared with other researchers to answer new research questions. In this sense, complete secrecy cannot be promised. Organizations such as the Institutional Review Board (IRB) that may inspect participant data and biological specimens.

## Interventions

### Explanation for the choice of comparators {6b}

The comparator is stretching that is matched to cycling duration, but at light intensity (≤ 30% of heart rate [HR] reserve [HRR] or rating of perceived exertion [RPE] ≤ 9). HRR is determined based on the peak cycle-ergometer exercise test during screening as the difference between peak and resting HRs. This comparator group was selected to equalize staff-participant interactions without affecting aerobic fitness.

### Intervention description {11a}

The initial aerobic exercise intervention is MICT on recumbent stationary cycles. The dose of MICT is prescribed as 50–75% of HRR and 9–14 RPE and starts at 50–60% of HRR or RPE 9–11 for 30 min. Cycling intensity and duration is alternatively increased by 5% of HRR (or 1-point on the RPE) or 5-min increments as tolerated up to 65%–75% of HRR (or RPE 12–14) for 50 min a session over time.

### Criteria for discontinuing or modifying allocated interventions {11b}

After 3 months of MICT, aerobic fitness non-response is determined in a three-hierarchical order as (1) < 5% increase in VO_2peak_ if peak cycle-ergometer exercise test with indirect calorimetry is completed at sufficient effort (e.g., respiratory exchange ratio ≥ 1.0 or HR ≥ 85% of the age-predicted max HR). (2) If exercise test is refused (e.g., participant wishes not to wear testing mask), non-response is indicated by < 10% increase in peak aerobic power (peak watts/kg) on the exercise test. (3) For participants who do not complete the exercise test, non-response is indicated by < 36.5-m increase in the distance of shuttle walk test (SWT). Non-responders are re-randomized 1:1 to HIIT or CARE for 3 months, stratefied by baseline age and random permuted blocks of 3 and 6. Responders continue MICT for 3 more months.

HIIT. An evidence-based “Scandinavian-style” HIIT protocol is used [22, 23]. This protocol includes 40 min of HITT comprising 5 sets of 4-min high-intensity cycling followed by 4-min moderate-intensity cycling. After a 10-min warm-up, participants progress to moderate intensity before the first set of HIIT. High intensity is prescribed as 80–85% HRR or RPE 15–16 for the first 8 weeks and increased to 80–90% HRR or RPE 15–17 after week 8. Following the HITT session, a 10-min cool-down period is conducted.

CARE. CARE includes 20-min resistance exercise followed by 30-min cycling. Resistance exercises target six major muscle groups (chest press, shoulder press, squats, rows, leg press, calf raises), are performed on exercise machines, and are adapted for any mobility or musculoskeletal issues reported by participants. Intensity is based on estimated one-repetition maximal strength (1RM) and progress following guidelines for older adults [24]. It starts with 2 sets of 10–12 repetitions at moderate intensity (50–60% 1RM, 9–11 RPE) and progressively increases to 70–85% 1RM or 13–16 RPE by week 7. Rest intervals are 1–2 min between sets. Cycling intensity is 65–75% HRR or RPE 12–14, like exercise prescription used during the MICT.

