### Sample size {14}

Assuming 18% attrition at 6 months and 25% attrition at 12 months, the sample size of 108 participants should result in a population of *n* = 89 at 6 months and *n* = 81 at 12 months. Under H1a, tests comparing participants assigned to MICT vs. control at R1, 89 complete cases (60 intervention [MICT, MICT + HIIT, MICT + CARE]; 29 control) at 6 months should result in 80% power to detect significant between-group differences in VO_2peak_ and WMHv changes, assuming a standardized between-group difference of *d* = 0.65 (based on a clinically meaningful difference in VO_2peak_ of 3.12 mL/kg/min) and SD = 4.8 (derived from previous research [49]), a pre-post correlation (*r*) in VO_2peak_ of 0.50, and *α* = 0.05 [50]; at 12 months, 81 complete cases (54 intervention; 27 control) should result in 80% power to detect differences of *d* ≥ 0.60, assuming pre-post *r* of 0.50 and *α* = 0.05. For models under H1b, 89 complete cases at 6 months should result in 80% power to detect between-group differences in change of *d* ≥ 0.57 for memory, quality of life (QoL), physical function, and behavioral and psychological symptoms of dementia (BPSD) scores, assuming pre-post *r* of 0.50 and *α* = 0.05; at 6 and 12 months, 81 complete cases should afford power to detect differences in change of *d* ≥ 0.60. For H2a, simulations conducted in R with the latest version at the time of data analyses (20,000 replications for each of 7 effect size scenarios) indicate that tests for a monotonic ordering of group means (i.e., MICT + HIIT > MICT + CARE > MICT > stretching) on VO_2peak_ should have power ≥ 80% for orderings comprising small MICT + HIIT vs. MICT + CARE and MICT + HIIT vs. MICT differences (*d*s = 0.25–0.35) and moderate MICT only vs. stretching differences (*d*s = 0.40–0.55). For H2b, assuming *n* = 13 per group, logistic-regression models are 80% powered to detect large between-group (MICT + HIIT vs. MICT + CARE) differences in number of responders (vs. non-responders), e.g., ≤ 2 non-responders in MICT + HIIT vs. ≥ 11 non-responders in MICT + CARE at *α* = 0.05. For H3, potential mediation of exercise effects (**X**: MICT [*n* = 59] vs. control [*n* = 30]) on memory (**Y**s) through AD/ADRD plasma biomarkers (**M**s) is ≥ 80% powered to detect mediated effects comprising modest direct associations (*r*^2^s ≥ 0.12) between groups (at R1) and each putative mediator (X → M link) and between each mediator and memory (M → Y link) [51].

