## Assignment of interventions: allocation

### Sequence generation {16a}

Prior to recruitment, the statistician created 2 randomization schedules using random permuted blocks of 3 and 6 participants in the study’s Research Electronic Data Capture (REDCap) system.

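### Blocks of 3 cannot deliver the stated 1:1 HIIT:CARE re-randomisation, and the written age strata omit eligible 65-year-olds; check the loaded schedule and correct the text

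*Protocol article*

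**What the plan says.** Trial design {8} sets two ratios. At the first randomisation, participants "are randomized using a 2:1 allocation ratio (randomization 1) to 3-month MICT or 6-month stretching control". For the second, it says: "Non-responders are subsequently re-randomized on a 1:1 allocation ratio to either HIIT or CARE for 3 months (randomization 2". The Abstract and section {11b} repeat the 1:1 ratio.

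The same block sizes are attached to both. Trial design {8}: "Both randomizations are stratified by baseline age (66–75, 76–85, 85 + years) using random permuted blocks of 3 and 6". Section {11b} repeats them for the re-randomisation alone: "Non-responders are re-randomized 1:1 to HIIT or CARE for 3 months, stratefied by baseline age and random permuted blocks of 3 and 6". Sequence generation {16a} says that, before recruitment, "the statistician created 2 randomization schedules using random permuted blocks of 3 and 6 participants" in REDCap. No section gives other block sizes for the second randomisation.

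Table 1 admits participants from age 65, with no upper limit. Sample size {14} plans the HIIT versus CARE comparison as follows: "For H2b, assuming *n* = 13 per group".

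**The concern.** A balanced permuted block must have a size that is a multiple of the sum of the ratio's terms. For 1:1 that means an even number, so the ratio and one of the two block sizes cannot both hold for the second randomisation. Because 3 and 6 are natural sizes for a 2:1 schedule, they may have been carried over from the first randomisation, either in the text or in the schedule itself.

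Separately, the age bands start one year above the eligibility limit, and two of them share the value 85. As written, there is no rule for filing a 65-year-old and no single rule for an 85-year-old. This part affects both randomisations.

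At stake is the HIIT versus CARE comparison under H2b, which rests on about 26 people. A reader cannot tell from the text what the allocation probability was. If the loaded schedule has the same fault, the trial is not delivering its stated 1:1 scheme.

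**Working it through.** **Inputs from the protocol article.** Randomisation 1 ratio 2:1, randomisation 2 ratio 1:1, and block sizes 3 and 6 for both ({8}, {11b}, {16a}); strata 66–75, 76–85, 85+ ({8}); eligibility from 65 (Table 1); 13 per group for H2b ({14}).

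**Planned figure.** 13 per group means 2 × 13 = 26 re-randomised, and 1:1 of 26 is 13:13. The planning figure agrees with the stated ratio.

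**Divisibility.**

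| Block size | At 2:1 | At 1:1 |
|---|---|---|
| 3 | 2 + 1, possible | 1.5 + 1.5, impossible |
| 6 | 4 + 2, possible | 3 + 3, possible |

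The stated sizes are right for randomisation 1. For randomisation 2, only size 6 works.

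**Age strata, applied literally.** Age 65: no stratum. Ages 66–75: one. Ages 76–84: one. Age 85: two (76–85 and 85+). Age 86 and over: one. If 85+ is read as over 85, the overlap goes but the gap at 65 remains.

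**What the block fault could do.** The article does not show the loaded schedule, so three readings were simulated: 26 people, 20,000 runs, sizes 3 and 6 equally likely. Stratum shares are an assumption (45/40/15%, with 50/40/10% as a check; the results barely differ). Imbalance is the absolute difference between the arm sizes. Relative information for a split a:b is (a × b / 26) ÷ (13 × 13 / 26), that is, ab/169.

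1. *Blocks of 3 randomly 2:1 or 1:2, blocks of 6 balanced.* Mean split 13:13, mean absolute imbalance about 1.9, 95th percentile 4. About 21% of runs differ by 4 or more. Average information is about 99% of 13:13.
2. *Every block of 3 tilted to the same arm, blocks of 6 balanced.* One block of each size gives 2 + 3 = 5 of 9 places to the favoured arm, and 26 × 5/9 = 14.4. The simulated mean is slightly higher, 14.6:11.4, because the strata are short. About 54% of runs differ by 4 or more. At the mean split, 14.6 × 11.4 / 169 = 0.985; averaged over runs, about 98%.
3. *The 2:1 ratio carried over in full.* 26 × 2/3 = 17.3 and 26 × 1/3 = 8.7, about 17:9. Information is 17 × 9 / 169 = 0.905; at exactly 2:1 it is 17.33 × 8.67 / 169 = 0.889.

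For comparison, blocks of 6 alone at 1:1 give a mean absolute imbalance of about 1.4.

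**The case against.** The strongest reply is that this may be a reporting slip. Section {16a} says that the schedules existed before recruitment, and Trial status says that recruitment opened in June 2023. A working schedule therefore exists, and nothing in the article shows that it is wrong. The 2:1 block sizes may simply have been copied into the description of the second randomisation. This stands, and it makes the check of the schedule the first step.

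It is also fair to say that the consequences are modest. Blocks of 3 in random direction give 1:1 on average, and two of the three readings keep about 98–99% of the information. A participant filed in either neighbouring stratum is still randomised; only the balance within strata suffers. The figure of 13 per group is a planning assumption that the non-response rate will shift in any case.

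A reader might go further and infer that the randomisation cannot be carried out, that the trial is running at 17:9, or that weights built on 1:1 are wrong. The article supports none of these. The loaded schedule is not visible. A 17:9 split needs the 1:1 ratio, stated three times, to have been ignored. The analysis sections specify generalised linear models, ordered contrasts and logistic regression, and mention no design weights. Age 85 in two strata is a literal reading; 85+ may mean over 85.

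The reply does not remove the contradiction. Three sections give the same block sizes, two of them expressly for the second randomisation, and the gap at age 65 remains under any reading. This is not a detail left to a fuller document: ratio, block sizes and strata are all stated, and they do not fit together.

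**Conclusion.** The text is wrong as written on two counts: size 3 is incompatible with the 1:1 HIIT:CARE allocation, and the strata do not cover every eligible age once. The block fault concerns randomisation 2 only; the strata fault concerns both. These conclusions need no assumption beyond the stated figures.

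The size of the effect is conditional on the loaded schedule. With 26 re-randomised and assumed stratum shares, it runs from a slightly looser balance around 13:13, through about 14.6:11.4, to about 17:9 with roughly 90% of the planned information. In none of these does the allocation itself bias HIIT versus CARE, since assignment remains random. If the schedule is already right, this is a correction of wording. If it is not, each further non-responder adds to the departure from the stated design.

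**What to change.** 1. While recruitment is open (planned to March 2027), the statistician checks the REDCap schedule for randomisation 2: block sizes, ratio within blocks, and how ages 65 and 85 are coded. The age coding of randomisation 1 should be checked as well.
2. If blocks of 3 or a 2:1 generator were loaded, replace the unused positions with even block sizes at 1:1, for example 4 and 6, or 6 alone. Keep the assignments already made. Report the actual allocation probabilities and account for them in the HIIT versus CARE analysis, because a correction in mid-trial makes the ratio differ between periods. Blocks of 2 are less attractive: every second assignment becomes predictable, and sections {16b}, {16c} and {17b} describe unblinded interventionists who may access the module and make assignments.
3. If the schedule is already correct, change only the text.
4. In either case, state block sizes separately for each randomisation in sections {8}, {11b} and {16a}. State age strata that cover every eligible age once, for example 65–75, 76–85 and 86 or older, matched to the coding in use.

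The cost is one check and a text correction or amendment, plus a schedule replacement if a fault is found. No additional participants are needed.
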